## Discussion

3

According to incomplete statistics, there were about 5.3 million patients with CP in China in 2018, and it is increasing at a rate of about 50,000 per year. The investigation report of children with CP in 12 provinces in China pointed out that the incidence of CP in children aged 1 to 6 years was 2.48‰, and the most common type of CP was spastic CP, which accounted for 58.86% of children with CP. Children with spastic CP are unable to stand, sit up and walk normally due to rigid extension reflexes, overexcited reflexes, and abnormal muscle stiffness, which is the main cause of severe motor disability in children.^[46]^ Children with CP are a huge group, and their treatment and rehabilitation is an important task in our country. Rehabilitation therapy plays a key role in the management of CP in children. It can help children with CP to maximize their potential for physical independence and health, and minimize the impact of physical injury. At present, the rehabilitation treatment of CP is mainly based on PT, including exercise therapy, hydrotherapy, occupational therapy, and tDCS. Among the outcome indicators such as motor function and balance function, it has been proven that hydrotherapy and tDCS are effective for children with CP. This study protocol describes a RCT study design which will test the comparative effectiveness of combining hydrotherapy and tDCS. The outcome evaluations will include analyses of GMFM-88, PBS. If the combination of hydrotherapy and tDCS is proven to be superior to the other in some of these aspects, this evidence would permit professionals to recommend the ideal PT for patients with CP, which will minimize their incapacity and optimize their rehabilitation. It is hoped that findings from this research will be published and disseminated in an internationally recognized, peer-reviewed journal.

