### Sample size

2.3

The necessary sample size has been estimated based on study of Whitehead et al,^[33]^ which estimated the minimum sample size of a pilot randomized trial with a continuous outcome variable. A previous RCT protocol about the effect of bilateral anodal tDCS vs treadmill training on brain activities of children with CP also used this Sample size estimation method. In our study, the Gross Motor Function Measure (GMFM) score which is a continuous outcome variable, is regarded as a primary outcome. The result is that 150 children with CP will undergo intervention or control group and will be assessed just once during pretest assessment to consider their results as a reference value for later comparisons. However, there is a lack of official pediatric reference values in GMFM of study on the combination of hydrotherapy and tDCS. Compared with the results of a meta-analysis, the sample size of our study is larger than that of each RCT on tDCS.^[34]^ Therefore, generalization of reference values from this study should be made with caution.

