### Evaluation and follow-up

2.5

Two experienced physical therapists who blind to which group each child belongs will evaluate the both group in the evaluation procedures. Four evaluations will be conducted:

First evaluation: 1 week before intervention;Second evaluation: 1 week after the last intervention;Third evaluation: 4 weeks after the last intervention;Fourth assessment: 12 weeks after the last intervention.These evaluations will be conducted on 2 nonconsecutive days.

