### Outcome measures

2.6

We will evaluate the CP children using questionnaires at the beginning of the treatment, within 1 week after 10 weeks of therapy, 4 weeks, and 12 weeks after the last intervention. Descriptive measures and characteristics, such as age, gender, body weight, type of CP and the outcomes were recorded for all study participants. All patient related data will be safely collected and stored. Only researchers related to the study will be allowed to access to the trial dataset. The primary outcomes of this study are Gross Motor Function Assessment and Pediatric Balance Scale (PBS) between the treatment group and the control group. The secondary outcomes are the difference in Pediatric Evaluation Disability Inventory (PEDI), adverse effects between the control and treatment groups.

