### Statistical analysis

2.8

An experienced statistician will conduct the data analysis. When necessary, intention to treat analysis will be used with the data from the previous evaluation repeated to substitute missing data. We will use the Kolmogorov-Smirnov test to demonstrate normal data distribution. Thus, Parametric data will be presented as mean (standard deviation) as well as nonparametric data will be presented as median (inter-quartile interval). The effect size will be calculated by the difference between means of the pre-intervention and post-intervention evaluations and will be presented with the respective 95% confidence interval. The independent *t* test and chi-square tests will be applied to assess and compare the baseline patient characteristics between the treatment and the control groups. Either 2-way ANOVA or the Kruskal-Wallis test will be used for the statistical analysis of the effects of control group or treatment group for parametric and nonparametric variables, respectively. The Bonferroni correction for multiple comparisons will be employed as the post hoc test. Statistical significance will be considered at a *P* value of <.05. The data will be organized and tabulated using the Statistical Package for the Social Sciences (SPSS) version 19.0 (IBM, Armonk, NY, USA).

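### With two unranked primary scales, no primary visit and an undefined Bonferroni family, the plan does not hold its overall false-positive rate at 5%

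*Protocol article*

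**What the plan says.** Section 2.6 (Outcome measures) names two primaries and does not rank them: "The primary outcomes of this study are Gross Motor Function Assessment and Pediatric Balance Scale (PBS) between the treatment group and the control group". Section 2.3 (Sample size) discusses only one of them: "the Gross Motor Function Measure (GMFM) score which is a continuous outcome variable, is regarded as a primary outcome".

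Section 2.5 (Evaluation and follow-up) sets three post-treatment evaluations: "Second evaluation: 1 week after the last intervention;Third evaluation: 4 weeks after the last intervention;Fourth assessment: 12 weeks after the last intervention". Neither it nor section 2.6 says which is primary. For PBS, section 2.6.1 mentions only administration before and after treatment, without saying which post-treatment visits are meant.

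Section 2.8 (Statistical analysis) plans a 2-way ANOVA, or a Kruskal-Wallis test for nonparametric variables, and adds: "The Bonferroni correction for multiple comparisons will be employed as the post hoc test". The threshold follows: "Statistical significance will be considered at a *P* value of <.05".

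The Discussion names GMFM-88 and PBS as the outcome evaluations. Its next sentence opens with "If the combination of hydrotherapy and tDCS is proven to be superior to the other in some of these aspects" and says such evidence would let professionals recommend the treatment.

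**The concern.** When success on any one of several tests can support the claim, a 5% threshold on each test does not give 5% for the trial. Here the number of tests is open in three ways: two scales, up to three visits, and a correction whose scope is not stated. A post hoc correction normally works inside one model for one outcome, and nothing in section 2.8 extends it across the two scales.

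The Kruskal-Wallis branch is looser still. That test has no time factor, so three visits would naturally mean three separate tests per scale. With only two groups there is a single pair, so a pairwise post hoc correction would have nothing to adjust.

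The hypothesis in the Introduction has two parts, a larger effect and a more durable one, and no visit is tied to either. What is at stake is a treatment recommendation for children resting on one favourable result among several, at an error rate the plan does not fix.

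**Working it through.** **Inputs from the protocol article**
- Per-test threshold 0.05 (section 2.8). Sidedness is not stated; two-sided is assumed.
- Primary scales: 2 (section 2.6).
- Post-treatment visits: 3 (section 2.5).
- Any scale may count (Discussion wording).

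**Assumed inputs.** The article gives no correlations. The main range used is 0.7 to 0.9 between visits and 0.3 to 0.7 between scales. Independence is shown as the upper limit.

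**Method.** For k independent tests at level a, the chance of at least one false positive is 1 − (1 − a)^k. For correlated tests, six standard normal statistics were simulated (500,000 draws). Their correlation matrix is the Kronecker product of a 2×2 scale matrix and a 3×3 visit matrix. The result is the share of draws in which any |Z| exceeds the critical value.

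**The plan's own figure.** One test gives 1 − 0.95 = 5.0%. The article states no familywise rate, so there is no other figure to reproduce.

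**Readings of the plan, two-sided**

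| Reading | Independent tests | With assumed correlations |
|---|---|---|
| One test per scale (2 tests at 0.05) | 1 − 0.95² = 9.75% | 8.3% to 9.5% (scales 0.7 to 0.3) |
| Bonferroni over 3 visits within each scale (6 tests at 0.05/3 = 0.0167) | 1 − (1 − 0.0167)^6 = 9.6% | 5.1% to 7.5% |
| Six tests, unadjusted (0.05 each) | 1 − 0.95^6 = 26.5% | 13.6% to 20.2% |
| Bonferroni over all six (0.05/6 = 0.0083 each) | 1 − (1 − 0.0083)^6 = 4.9% | 2.7% to 3.9% |

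In the last three rows the lower end is visits 0.9 and scales 0.7; the upper end is visits 0.7 and scales 0.3.

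**Sensitivity**
- With visits at 0.95 and scales at 0.8, the within-scale Bonferroni reading falls to 4.2% and the unadjusted reading to 11.3%.
- If PBS were taken at only one post-treatment visit, there would be four tests: 1 − 0.95⁴ = 18.5% if unadjusted and independent.
- Counting only errors that favour treatment, six unadjusted tests give 6.8% to 10.2% over the main correlation range (14.1% if independent). A single test gives 2.5%.

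**After the fix**
- One scale at one visit: 5.0%. Fixed-order testing after it adds nothing, because each later test is reached only if the one before is significant.
- Holm across two scales at one visit starts at 0.05/2 = 0.025: at most 5%, and 1 − 0.975² = 4.9% if independent.
- Naming one visit but leaving both scales unadjusted would still give about 8% to 10%.

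**The case against.** The strongest reply is that section 2.8 does plan a correction. If the 2-way ANOVA is group by time, Bonferroni can cover the visits, and the rate is then at most about double 5%. If its family spans all six comparisons, there is no excess. The ANOVA may also mean one decisive test per scale. Nothing in the article prescribes six visit-by-visit tests. All of this stands. A reader might infer that the plan has no error control, or that the rate is three times 5%. The text supports neither, because the family is undefined rather than absent, and the threefold figure needs six wholly unadjusted tests plus correlations the article does not give.

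The Discussion sentence is not a formal success rule and names no visits. That also stands. If success required both scales, there would be no inflation. But it is the only statement of what would count, it follows directly on the naming of the two scales, and it points to either one.

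A reader might also infer that section 2.3 contradicts section 2.6 by making GMFM the sole primary. It calls GMFM one primary outcome, using the indefinite article, which is compatible with two.

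Finally, an analysis plan not shown may define the Bonferroni family and the decisive contrast. For that reason it cannot be asserted that scale and visit will be chosen after seeing results. The primary endpoint and its timing are nevertheless protocol content. What the article does state (two unranked primaries, three visits, a per-test threshold, partial superiority sufficing) does not by itself hold the overall error at 5%.

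**Conclusion.** The concern holds as a failure to fix the primary scale, the primary visit and the scope of the Bonferroni correction. If a result on either scale counts, the two-sided false-positive rate is:

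- about 8% to 10% with one test per scale (between-scale correlation 0 to 0.7);
- about 5% to 10% with Bonferroni over visits within each scale, slightly lower at very high correlations;
- about 14% to 20% with six unadjusted tests (correlations 0.7 to 0.9 between visits and 0.3 to 0.7 between scales), rising to 26.5% under independence.

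Only a Bonferroni family covering all six tests is sure to keep it below 5%. The correlations and the two-sided level are assumptions, and it is not certain that PBS is measured at all three visits. The defect rests on the text itself; the size of the excess depends on which reading is used.

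**What to change.** In sections 2.6 and 2.8, name one primary endpoint: GMFM-88 total percentage score at one stated visit, for example 1 week after the last intervention, tested at two-sided 5%. Specify the total, because section 2.6.1 says the dimensions can be analysed separately or combined. Then test in fixed order, each step only if the one before is significant: PBS at that visit, GMFM-88 at 12 weeks (the durability part of the hypothesis), PBS at 12 weeks. Treat the 4-week results as descriptive. State which post-treatment visits include PBS, and say what the Bonferroni step covers, if it is kept.

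If both scales are to stay primary, apply Holm across GMFM-88 and PBS at that one visit instead.

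In the Discussion, replace the condition about partial superiority with wording tied to whichever rule is chosen.

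The cost is wording and a registry update. Under the fixed order, PBS cannot carry the trial if GMFM-88 fails. Under Holm, the smaller P value faces 0.025. With 75 per arm, power for a single scale at that threshold is 79% rather than 86% for a standardised difference of 0.5, and 58% rather than 69% for 0.4. Those differences are assumptions, since the article states none, and they show Holm at its strictest step.

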## Conclusion

4

In conclusion, this protocol describes an outcome assessor and data analyst-blinded, randomized, controlled superiority trial that aims to investigate the efficacy of a combined application of tDCS and hydrotherapy in patients with CP. The results will ascertain whether tDCS combined concurrently with hydrotherapy would result in the greater and longer-lasting improvement in motor function. The findings will be of great significance for clinical practice about treating CP.

## Ethics and dissemination

5

The trial will be commenced after ethical approval has been obtained from the Second Affiliated Hospital of Qiqihar Medical University. All study-related procedures will be performed only after obtaining written informed consent from children and their parents. Patients’ information will be collected, shared, and maintained in an independent closet to protect confidentiality before, during, and after the trial. The protocol has been registered at Chinese Clinical Trials Register, (http://www.chictr.org.cn/showproj.aspx?proj=128232, Identifier: ChiCTR2100047946).
